**Methods:**

In total, 192 participants aged 18-75 years with GPCI from the Mianyang Central Hospital, the Mianyang Hospital of Traditional Chinese Medicine, and the Mianyang Wanjiang Eye Hospital will participate in this study. Participants will be allocated to 2 treatment groups (experimental and control groups) in a ratio of 1:1 and will undergo press-needle therapy and sham press-needle therapy, respectively, for the same 4-week period. Primary outcomes will include the best-corrected visual acuity (BCVA), optical coherence tomography angiography (OCTA), color Doppler flow imaging (CDFI), and visual field assessment results. Secondary outcomes will include the intraocular pressure (IOP) and traditional Chinese medicine (TCM) clinical symptom scales. The primary outcomes and safety assessments will be measured at baseline and 4 weeks thereafter, while the secondary outcomes will be measured at baseline and 1, 2, 3, and 4 weeks thereafter.

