#### Criteria for Discontinuing or Modifying Allocated Interventions

Participants will have the freedom to withdraw from the clinical study and opt for alternative treatments (eg, citicoline sodium tablets) if they believe their condition will not improve. Reasons for discontinuing treatment may include, but are not limited to, the following: (1) the pregnancy, (2) severe side effects or complications, (3) taking other medications during the study, (4) failure to comply with the study protocol, and (5) request for withdrawal for other reasons.

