### Outcome Measures

#### Primary Outcome Measures

The primary outcomes will enable us to evaluate improvements in visual function, retinal blood circulation, and retrobulbar blood vessel circulation due to press-needle therapy. The outcomes will be as follows:

The mean change in the BCVA will be measured at baseline and 4 weeks thereafter.The mean change in the values of the pattern standard deviation (PSD), mean defect, and square root of loss variance (sLV) will be determined using an Octopus 900 perimeter at baseline and 4 weeks thereafter.The whole-image vessel density (wiVD), radial peripapillary capillary vessel density (RPCVD), superficial macula vascular density (smVD), parafoveal vessel density (paraVD), perifoveal vessel density (periVD), macular ganglion cell complex (mGCC), and peripapillary retinal nerve fiber layer (pRNFL) will be determined using optical coherence tomography angiography (OCTA) at baseline and 4 weeks thereafter.The ophthalmic artery (OA), central retinal artery (CRA), short posterior ciliary artery (SPCA), peak systolic velocity (PSV), end diastolic velocity (EDV), and resistance index (RI) will be determined using CDFI at baseline and 4 weeks thereafter.

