### Data Collection and Quality Control

Thorough recording of all data will be performed on CRFs subsequent to in-person visits or telephonic communications with participants. The same examiner will assume responsibility for conducting the examination of every patient during each assessment. Baseline measurements, demographics, medical history, and prior medications will only be gathered during the initial visit. Primary outcomes, secondary outcomes, and safety indicators will be gathered at baseline and 4 weeks thereafter. Following adequate training and successful completion of a test, 2 data entry clerks will thoroughly review the CRFs and subsequently enter the collected data independently. Participants’ personal information will be kept confidential the same way as their medical histories in the hospitals before, during, and after the trial. The absence of a data monitoring committee in this study is justified by the anticipated low incidence of AEs and the limited participant numbers at each center. The Epidata 3.1 statistical application will be used for data entry. Subsequently, the collected data will be transferred to IBM SPSS 22.0 statistical software for the purpose of analysis.

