### Sample Size Calculation

The sample size calculation was based on previous studies. The basis of optic nerve protection effectiveness is 70% [16,17]. We hypothesized an 80% effective rate of the basis of optic nerve protection + press needles for GPCI in a larger sample size. According to the sample size of the estimation formula [18], α=.05 and β=0.10 in a 2-sided test, *P*_1_=.67 and *P*_2_=.87, 2-sided u_α/2_=u_0.05/2_=1.96, and 1-tailed u_β_=u_0.1_=1.282. We substituted these values into the following formula:

This resulted in n^1^=n^2^=79.02, that is, approximately 80 cases each in the experimental and the control group, or 160 cases in both groups. To account for a 20% dropout rate, the calculation 160 + (160 × 20%) = 192 suggested that 192 patients be recruited.

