### Statistical Analysis

Statistical analysis will be conducted independently by statisticians. The data will be presented as means (SDs). IBM SPSS 22.0 statistical software will be used. All statistical tests will be 2-sided tests, and the limit for statistical significance will be set at *P*<.05. The chi-square test will be performed for categorical variables, the independent Student *t* test will be used for measurement data, and the rank-sum test will be used for grade data. To evaluate the covariate balance, baseline characteristics will be summarized and compared between the experimental group and the control group using simple descriptive statistics.

Due to the expected low number of missing data, we will deal with missing data by transferring the last data item to the final dataset. This participant's data will be invalidated in the full analysis set (FAS), and this case will not be included in the per protocol set (PPS). Finally, the statistical significance of the FAS and PPS will be analyzed. A consistent statistical significance will indicate a significant difference.

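### Carrying the last value forward gives a participant with no week-4 primary measurement a change of zero, and the next sentence of the plan invalidates the same data in the FAS

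*Protocol article*

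**What the plan says.** - **Missing-data rule (Protocol article, Statistical Analysis).** The rule is "we will deal with missing data by transferring the last data item to the final dataset". The stated reason is that few data are expected to be missing. The next sentence says the participant's data will be invalidated in the FAS and the case left out of the per-protocol set (PPS). The section ends by requiring consistent significance across the two sets.
- **Primary visits.** The Abstract (Methods) states: "The primary outcomes and safety assessments will be measured at baseline and 4 weeks thereafter". Primary Outcome Measures agrees: "The mean change in the BCVA will be measured at baseline and 4 weeks thereafter", and the perimetry values "will be determined using an Octopus 900 perimeter at baseline and 4 weeks thereafter". OCTA and CDFI have the same two time points. No early-termination measurement is described.
- **Secondary visits.** According to the Abstract, "the secondary outcomes will be measured at baseline and 1, 2, 3, and 4 weeks thereafter". Secondary Outcome Measures gives the same weekly schedule for IOP and the TCM symptom score.
- **Amount of dropout.** Sample Size Calculation raises 160 to 192 "To account for a 20% dropout rate". The Results report 192 of 220 recruited participants (87.3%) as those who will complete.

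**The concern.** Carrying a value forward needs a later value to carry. With two time points there is none, so the rule amounts to imputing the baseline value. For an outcome analysed as change, that inserts a zero and counts it as an observed result. The FAS estimate then mixes the effect in those measured with zeros for those not measured. If dropout differs between arms and both arms change over the four weeks, the zeros alone produce a difference.

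The sentence that follows is a second problem. Data cannot be both filled in and invalidated in the same analysis set. One reading gives an FAS containing zeros, the other an FAS without these participants. The plan does not say which applies.

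The reason given for the rule also sits badly with the plan's own figures. A trial that adds participants for 20% dropout is not obviously one with few missing data.

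**Working it through.** **Inputs from the document.** There are 192 participants allocated 1:1, so 96 per arm. Primary outcomes are measured at baseline and week 4. Measurement data are compared by an unadjusted t test at two-sided 0.05.

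**The plan's dropout figure.** 160 + (160 × 20%) = 192 reproduces. The 32 added are 32/192 = 16.7% of those recruited. In the Results, 28 of 220 do not complete, which is 12.7%.

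**Assumptions, because the document gives none for the primary outcomes.** The SD of change is 1. Dropout is unrelated to outcome. The PPS consists of the completers. Mean changes and dropout by arm are as stated in each case.

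**Formulas.** Let an arm have mean change μ and dropout d, with dropouts scored zero.
- Expected mean change: (1 − d)μ
- Variance of one change score: (1 − d) + d(1 − d)μ²
- SE of the difference: square root of (sum of the two variances / 96)
- SE from completers only: square root of (2 / (96(1 − d)))

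**Case 1: equal dropout, true effect 0.50 SD (control 0, treated 0.50).**
- *20% dropout.* Estimate = 0.8 × 0.50 = 0.40. Variances are 0.80 and 0.80 + 0.16 × 0.25 = 0.84. SE = √(1.64/96) = 0.131. Completers give √(2/76.8) = 0.161. Simulated coverage of the true 0.50 by the carry-forward interval is about 88%, against 95% for completers.
- *12.7% dropout.* Estimate = 0.873 × 0.50 = 0.44. SE = 0.136, against 0.154 for completers. Coverage is about 92% to 93%.
- *Power at 20%.* About 86% with carry-forward and 86% to 87% with completers, because estimate and SE shrink together. With no true effect, rejection stays at 5%.

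**Case 2: no true effect, dropout 10% and 30%, both arms changing by the same amount.**

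| Common change | False FAS difference | FAS test alone rejects | PPS test rejects | Both reject |
|---|---|---|---|---|
| 0.5 SD | (0.9 − 0.7) × 0.5 = 0.10 SD | about 12% | 5% | about 3% |
| 1 SD | (0.9 − 0.7) × 1 = 0.20 SD | about 29% to 30% | 5% | about 2.5% |

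Coverage of the FAS interval in these two rows is about 88% and 71%.

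**Sensitivity to the amount missing.** At 5% missing, the carry-forward SE is 0.95 to 0.97 of the completers' SE for mean changes up to 1 SD, so the effect is slight. At 20% the ratio is 0.80 to 0.88.

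**The case against.** Several points on the other side stand.

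1. **The invalidation sentence.** Read literally, it removes the dropout from the FAS, and no zero enters any test. It is then wrong to say that every dropout is scored as zero change. That is one of two readings, and the text does not settle which.

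2. **False positives.** A reader might infer from the FAS-only rejection rates of 12% to 30% that the trial's type I error is inflated. The plan does not support that. It asks for consistent significance in FAS and PPS, and under that rule joint rejection is below 5% in both cases above. What remains is a biased FAS estimate and interval.

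3. **Standard errors.** A reader might infer that the carry-forward SE is simply wrong. It is not: at 20% dropout it averages 0.130 to 0.131, and the estimator's own sampling SD is 0.130 to 0.131. It is smaller than the observed data support for the true effect, but the undercoverage comes mainly from the shrunken estimate.

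4. **Informative dropout.** The discontinuation criteria include "3) taking other medications during the study, (4) failure to comply with the study protocol", and participants may leave if they believe they will not improve. It is tempting to conclude that missingness depends on outcome. That is plausible, but the section lists reasons for stopping treatment and does not say that week-4 measurement stops. The figures above do not rely on it.

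5. **Scope.** Change is named explicitly only for BCVA and perimetry. If OCTA and CDFI are compared as week-4 values, carrying baseline forward still shrinks the expected difference by the factor (1 − d), but it does not insert a constant, so the SE figures above do not apply. The weekly secondary outcomes have later values to carry and are not affected in this form.

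6. **Inputs.** The 10% and 30% split and the common change are illustrations. The document gives no dropout by arm.

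**Conclusion.** The concern holds in limited form. The rule does not suit a two-visit primary outcome, and it conflicts with the sentence that follows it. If values are carried forward, the FAS effect is diluted in proportion to dropout: 0.50 SD becomes about 0.40 SD at 20% and about 0.44 SD at 12.7%, with interval coverage of about 88% and 92% to 93%. If dropout differs by arm and both arms change, the FAS can show a false difference, of 0.10 to 0.20 SD under the illustrated assumptions. The damage is to the reported FAS estimate and interval. The final yes/no conclusion is largely protected by the requirement that FAS and PPS agree, taking the PPS to be the completers. The effect sizes assume SD-scaled changes and dropout unrelated to outcome; at 5% missing they would be small.

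**What to change.** In Statistical Analysis:

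- Replace carry-forward for the primary outcomes with multiple imputation under missing-at-random, done by arm, with baseline value, glaucoma stage and the weekly IOP and TCM scores as predictors. Add one sensitivity analysis that departs from missing-at-random.
- Rewrite the invalidation sentence so that all randomised participants are analysed in the FAS, and state separately who leaves the PPS.
- Reconcile the expectation of few missing data with the 20% dropout allowance in Sample Size Calculation.
- Confirm the weekly schedule on which the imputation relies. Data Collection and Quality Control says "Primary outcomes, secondary outcomes, and safety indicators will be gathered at baseline and 4 weeks thereafter", without mentioning weeks 1 to 3.

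The cost is some extra analysis work and, under Ethical Considerations, a submission to the ethics committee for the changed analysis. No new data are needed. The Discussion keeps statisticians blinded until database lock, so a change made before then can be fixed without knowledge of results.

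### The missing-data rule contradicts itself; read literally, it removes participants with missing data from both the FAS and the PPS, so agreement of the two sets cannot test sensitivity to missing data

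*Protocol article*

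**What the plan says.** All references are to the protocol article.

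- **Statistical Analysis, missing data.** The method is single imputation: "we will deal with missing data by transferring the last data item to the final dataset". The reason given is "Due to the expected low number of missing data".
- **Statistical Analysis, analysis sets.** The next sentence says that this participant's "data will be invalidated in the full analysis set (FAS), and this case will not be included in the per protocol set (PPS". Neither set is defined. No intention-to-treat set or other analysis of all randomised participants is named.
- **Statistical Analysis, conclusion.** Both sets are tested, and "A consistent statistical significance will indicate a significant difference".
- **Criteria for Discontinuing or Modifying Allocated Interventions.** Participants may withdraw and "opt for alternative treatments (eg, citicoline sodium tablets) if they believe their condition will not improve". Use of other medication and failure to follow the protocol are also listed as reasons for discontinuing.
- **Sample Size Calculation.** "To account for a 20% dropout rate, the calculation 160 + (160 × 20%) = 192 suggested that 192 patients be recruited".
- **Primary Outcome Measures.** Primary outcomes are measured at baseline and at week 4 only.
- **Abstract and Results.** 220 participants had been recruited, of whom 192 (87.3%) are described as those who will complete.

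**The concern.** Carrying a value forward is useful only if the participant stays in an analysis set. Here the participant is imputed, then made invalid in one set and left out of the other. Two statisticians following this paragraph could analyse different people.

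If the second sentence governs, both sets consist of completers. Withdrawal is open to participants who think they are not improving, so dropout may depend on outcome. A comparison of completers then no longer rests on randomisation. Agreement between FAS and PPS would look like a robustness check, but the same people would be absent from both.

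If the first sentence governs, there is a different problem. With no measurement of the primary outcomes between baseline and week 4, the last value is the baseline value, so a dropout is recorded as having changed by exactly zero.

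**Working it through.** **1. How many participants are affected.** The plan's allowance reproduces as arithmetic: 160 + 160 × 0.20 = 192. Twenty per cent of those randomised is 192 × 0.20 = 38.4, leaving 192 × 0.80 = 153.6, or about 77 per arm at 1:1. That is hard to square with an expectation of few missing data. From the Results, 220 − 192 = 28 are not counted as completing, and 28/220 = 12.7%.

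**2. Bias of a completers-only comparison.** Assume no true effect and a normal outcome. One arm loses its lowest fraction d and the other loses d at random. The remaining mean in the first arm is shifted by φ(z_d)/(1 − d) SD, where z_d is the normal quantile at d.

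| d | φ(z_d) | Bias (SD), formula | Bias (SD), simulated | P<.05, simulated |
|---|---|---|---|---|
| 20% (19 of 96 per arm) | 0.280 | 0.280/0.80 = 0.35 | 0.34 | 65% |
| 12.7% (14 of 110 per arm) | 0.208 | 0.208/0.873 = 0.24 | 0.24 | 43% |
| 12.7% (12 of 96 per arm) | 0.208 | 0.24 | 0.23 | 38% |
| 5% (assumed; 5 of 96 per arm) | 0.103 | 0.103/0.95 = 0.11 | 0.11 | 13% |

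Each simulation used 20,000 runs and the two-sided *t* test named in the plan. The sign depends on which arm loses its worst patients; the arm that loses them looks better. If both arms lose their worst 20%, the bias is zero, though the test still rejects in about 11% of runs. If dropout is unrelated to outcome, the bias is zero.

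**3. What the reading of the rule changes.** For illustration, take the rates entered in the sample size formula (0.67 and 0.87), 96 per arm and 20% dropout unrelated to outcome. Power = Φ{[|p₂ − p₁|√n − 1.96√(2p̄q̄)] / √(p₁q₁ + p₂q₂)}.

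- All 192 with complete outcomes: (0.20 × √96 − 1.96 × 0.595)/0.578 = 1.37, power 0.91.
- Dropouts removed, n = 76.8 per arm: (0.20 × √76.8 − 1.96 × 0.595)/0.578 = 1.01, power 0.84.
- Dropouts kept and counted as not effective: the rates become 0.67 × 0.8 = 0.536 and 0.87 × 0.8 = 0.696; (0.16 × √96 − 1.96 × 0.688)/0.678 = 0.32, power 0.63.

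The stated inputs give about 91 per group by this formula rather than the article's 79.02. That is a separate matter and does not affect this point.

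**4. What FAS–PPS agreement can show.** Under the same assumptions, a 40,000-run simulation gives the share of trials in which the two sets disagree on significance:

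- Dropouts removed from both, no other PPS exclusions: 0%, because the sets are identical.
- Dropouts removed from both, with a further 5% or 10% of completers leaving the PPS for deviations (assumed): 4.5% or 7.3%.
- Dropouts counted as not effective in the FAS: 25% to 26%.

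**5. If carry-forward governs instead.** With dropout at rate d in both arms, unrelated to outcome, each dropout contributes zero change. A true difference δ in mean change is therefore estimated as (1 − d)δ, which is 0.8δ at 20%.

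**The case against.** The strongest defence is that exclusion from the FAS is not established. The sentence uses different verbs for the two sets, and carry-forward has a purpose only if the case stays somewhere. The sample size rests on an effective rate, so *invalidated* might mean counted as not effective, and the FAS would then hold everyone. This stands as a possible reading. A reader might therefore infer from the paragraph that no all-randomised analysis exists, and the text does not support so firm a statement. But the alternative is not stated either, and it fits poorly with primary outcomes that are mean changes and continuous measurements with no responder definition.

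A reader might also infer that the consistency rule checks nothing. That goes too far. The PPS may exclude participants for other medication or non-compliance, and then the rule says something about those deviations. What it cannot do, under the literal reading, is test sensitivity to missing data.

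The rule has a natural reading when the sets differ, namely that no difference is claimed. Requiring both to be significant cannot produce more false positives than either set alone. That is correct, but it gives no protection when both sets carry the same bias.

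On size, participants are blinded to a similar-looking sham and the withdrawal rule is the same in both arms, so nothing in the article shows that dropout will differ by arm. The 20% is a recruitment allowance. The 28 of 220 are not shown to be dropouts; the Abstract even assigns the remainder to exploratory work. These points stand, which is why the bias figures are an assumed extreme and not a forecast.

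**Conclusion.** The paragraph contradicts itself and must be corrected, because it decides who enters the primary comparison. This is a rule the article states, not detail left to an analysis plan. Taken literally, both sets omit everyone with missing data, no analysis of all randomised participants is stated, and agreement of the sets is uninformative about dropout.

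The possible bias ranges from zero (dropout unrelated to outcome, or alike in both arms) to about 0.24 SD at 12.7% loss and 0.34 SD at 20%. The upper figures require one arm to lose exactly its worst patients while the other loses at random. The documents support neither the claim that this will happen nor the claim that completers-only sets are the only possible reading. The contradiction itself does not depend on those assumptions.

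**What to change.** - Delete the invalidation wording. Define the FAS as all randomised participants, analysed in the arm assigned, including those without week-4 data.
- State one missing-data method for the FAS, and not the carrying of baseline to week 4. Examples are a baseline-adjusted likelihood model, or multiple imputation using baseline, glaucoma stage and the weekly secondary measures. For the last of these, confirm the schedule first: Secondary Outcome Measures lists weeks 1 to 4, while Data Collection and Quality Control lists only baseline and week 4.
- Add a sensitivity analysis for outcome-related dropout that can differ by arm.
- Base the primary conclusion on the FAS. Define the PPS by listed protocol deviations, keep it as supportive, and replace the consistency rule accordingly.
- Reconcile the expectation of few missing data with the 20% allowance.

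The cost is a few reworded sentences and slightly more analysis work, with no new data. Under Ethical Considerations, a change to the analyses goes to the ethics committee as a new protocol version. It should be made before database lock; the Results section places analysis in October 2025.

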## Results

The study flowchart is shown in Figure 2. The figure also presents an outline of the case distribution across each center, as well as comprehensive outline of precise measurements and designated data collection time points. Recruitment was conducted from February 2023 to March 2024. The first participant was enrolled in February 2023. As of October 2024, the project had recruited 220 eligible participants. At the time of submission, there were 192 (87.3%) participants, who will complete the study. The recruitment process is expected to continue until September 2025. The data will be further processed and analyzed in October 2025.

